### Outcomes

#### Primary outcome

The primary outcome is change in medication adherence (continuous variable for percentage of medication doses taken on time) measured by electronic medication monitors after each intervention. We will also measure adherence by three additional techniques in order to reflect different aspects of adherence behavior [51] and compare the techniques to one another: (a) video-recorded drop instillation, (b) self-reported adherence [52–55], and (c) pharmacy refill data. To assess how well patients can properly instill their eye drops, we will video-record patients instilling their eye drops during their third and fifth study visits, before and at the end of the eyeGuide intervention, respectively. Two masked assessors will review the videos and assess each participant for the following three techniques: (1) does the participant dispense a single drop, (2) does the drop get into the eye, and (3) does the participant touch the dropper tip to the ocular adnexa or extraocular structures. Self-reported adherence will be assessed with the Morisky questionnaire [56] (eight items, Cronbach *α* = 0.83), the Adherence to Refills and Medications Scale [57] (ARMS, 12 items, *α* = 0.81), and three additional questions about adherence from the glaucoma literature [55, 51]. These adherence questionnaires will be given at the baseline, 3-, 6-, 12-, and 24-month study visits.

Pharmacy refill data will be obtained by calling each participant’s pharmacy every 3 months to identify whether each prescribed medication has been filled. The medication possession ratio (MPR) is the proportion of days during a fixed time period where the patient had an adequate supply of medication to use at the prescribed frequency. MPR will be calculated at the patient level after combining refill data from all medications during a defined time period, as follows:$$ \frac{\mathrm{MPR}=\kern0.5em \#\mathrm{days}\ \mathrm{correct}\ \mathrm{amount}\ \mathrm{of}\ \mathrm{medication}\ 1+\dots +\#\mathrm{days}\ \mathrm{correct}\ \mathrm{amount}\ \mathrm{of}\ \mathrm{medication}\ 4}{\#\mathrm{elapsed}\ \mathrm{days}\ \mathrm{medication}\ 1+\dots +\#\mathrm{elapsed}\ \mathrm{days}\ \mathrm{medication}\ 4} $$

In this study, MPR will be calculated during fixed, quarterly time intervals of 91–92 days from enrollment, as well as cumulatively over each intervention period. The participants’ pharmacies will be called after a quarter has been completed to obtain refill information (date of fill, medication dispensed, day’s supply, number of mLs dispensed). In the event of overlapping refills, it will be assumed that medications are taken sequentially, not doubly dosed, to avoid an MPR greater than 1.

#### Secondary outcomes

Secondary patient outcomes include changes in clinical outcomes, changes in psychosocial mediators of adherence, and intervention impact on patient satisfaction. Our clinical outcome is IOP and IOP fluctuation [58], which will be measured during each study visit and collected from clinic visits that participants have during the study period (expect 7–9 measurements from study visits and clinic visits). IOP will be checked at each in-person study visit using Goldmann applanation tonometry. Any additional IOP measurements taken during clinic visits during participants’ time in the study will be abstracted from the electronic health record.

The two psychosocial mediators of adherence in our theoretical model (Fig. 1) include (1) change in perceived *glaucoma skills* (perceived competence [59]), glaucoma knowledge [60], glaucoma medication and eye drop instillation self-efficacy [61], goal setting [62], and propensity to ask questions of their physician [63]) and (2) change in *energy for change* (motivational state [64] and autonomy [65]) after each intervention. We will also assess the intervention’s impact on patient satisfaction (satisfaction with information about glaucoma [66] and client satisfaction [67, 68]).

Validated measures will be used to assess these proposed mediators of adherence. Skills will be measured with five constructs: perceived competence, glaucoma knowledge, self-efficacy, goal setting, and confidence asking the physician questions. Perceived competence [59] (four items, Cronbach *α* = 0.80) assesses participants’ perceptions of how able they are to manage their glaucoma on a seven-point Likert scale. Perceived competence will be measured at the baseline, 6-, 12-, and 24-month study visits. Glaucoma Knowledge will be assessed with a 10-item true/false test generated by the National Eye Institute (NEI) [60]. Glaucoma knowledge will be measured at the 3- and 8-month study visits, before and after the eyeGuide intervention, respectively, and at the 24-month study visit. Glaucoma medication and eye drop instillation self-efficacy [61] (medication self-efficacy, 10 items, eye drop instillation self-efficacy, 6 items, *α* = 0.91 for all 16 items) assess participants’ self-confidence in using their eye drop medications as prescribed and instilling them into their eyes correctly using a three-point Likert scale. Glaucoma medication and eye drop instillation self-efficacy will be measured at the baseline, 6-, 12-, and 24-month study visits. Goal setting (three items, *α* = 0.80) measures whether or not health care providers asked participants to set goals to improve how they take care of their chronic disease on a five-point Likert scale. The Goal Setting Scale is a sub-scale of the Patient Assessment of Chronic Illness [62] measure. We could not use the full sub-scale as the final two questions ask if the person has been asked to attend a class to help cope with their chronic condition or asked to fill out a survey about their chronic condition, neither of which are standard aspects of current glaucoma care. Goal setting will be measured at the baseline study visit, and the 12- and 24-month study visits. Confidence asking the physician questions will be measured with three items from the adapted Perceived Efficacy in Patient-Physician Interactions Scale [63] (PEPPI, five items, α = 0.83) using a five-point Likert scale. Confidence asking the physician questions will be assessed at the baseline visit and the 12-month study visit.

Energy for change will be measured with two constructs using two different scales, the Health Care Climate Questionnaire [65] (HCCQ; 12 items, *α* = 0.96) and the Treatment Self-Regulation Questionnaire [64] (TSRQ; 19 items, *α* = 0.81). The HCCQ measures perceived autonomy support from health care providers. The TSRQ measures whether a participant feels motivated to accomplish a health-related goal because of their own internal desires, such as “I personally believe that controlling my glaucoma will improve my health” or whether they take care of their health problem for reasons external to themselves, like “I want my doctor to think I’m a good patient.” Both of these scales have been validated in patients with diabetes and have been adapted to glaucoma, a similar chronic disease that requires consistent self-management for optimal disease control, for this study. Both scales use seven-point Likert scales. The HCCQ and TSRQ will both be given at the baseline, 6-, 12-, and 24-month study visits.

Satisfaction will be measured in two ways. Satisfaction with information about glaucoma will be measured using the Satisfaction with Information Scale [66] (four items). These questions were developed to assess how patients with hyperlipidemia felt about the type of information they received about their disease. The scale uses a seven point Likert scale to assess satisfaction with the amount of information received, the clarity of the information, how helpful the information was, and how well people now understood how to take their medications. The Satisfaction with Information scale will be given at the baseline study visit, and the 12-month study visit, at the conclusion of the eyeGuide intervention. Satisfaction with the eyeGuide intervention will also be measured at the 12-month study visit using the Client Satisfaction Questionnaire [67, 68] (three-item subscale, *α* = 0.91).

We will explore the effect of possible moderators and mediators of glaucoma medication adherence, such as total number of minutes of counseling, socio-demographic characteristics, visual function [69], health literacy [70, 71], severity of glaucoma, glaucoma symptoms [72], number of prescribed classes of glaucoma medications, medical co-morbidities, perceived stress [73], consideration of future consequences [74], barriers to glaucoma medication adherence [75], social support [76], depression [77, 78], glaucoma-related distress [79], hopefulness, confidence and motivation to manage glaucoma [32], and perceived benefit to glaucoma treatment [80]. These constructs will be measured using validated instruments or particular items from validated instruments to assess specific variables (Table 2). We will also explore the acceptability of and satisfaction with each level of the intervention through semi-structured interviews with participants. All participants will be interviewed with a semi-structured interview guide (Additional file 3). The number of minutes of counseling recorded alongside amount of booster training given will be used as an estimate of potential labor force costs to implementing the counseling program in the clinical setting.

**Table 2 Tab2:** Scales for potential moderators and mediators of glaucoma medication adherence for exploratory analysis

Moderators	Mediators	Time point^a^	Original source
Visual function		1	National Eye Institute Visual Function Questionnaire (Mangione 2011)
Functional health literacy		1	Functional Health Literacy (Chew 2004)
Health literacy		2	Rapid Estimation of Adult Literacy in Medicine (Arozullah 2007)
Glaucoma symptoms		1	Glaucoma Symptom Scale (Lee 1998)
Perceived Stress		1	Perceived Stress Scale (Cohen 1983)
Consideration of future consequences		1	Consideration of Future Consequences Scale (Strathman 1984)
	Glaucoma-related distress	1, 3, 5, 6	Diabetes Distress Scale (Polonsky 2005)
	Barriers to glaucoma medication adherence	1, 3, 5, 6	Glaucoma Treatment Compliance Assessment Tool (Barker 2015)
	Social support	1, 5, 6	Diabetes Specific Social Support Needs (Rosland 2008)
	Depression	2, 5, 6	Patient Health Questionnaire-9 (Kroenke 2001)
	Hopefulness, confidence and motivation to manage glaucoma	1, 3, 5, 6	Hopefullness, Confidence and Motivation Rulers (Miller and Rollnick 2012)
	Perceived benefit to Glaucoma Treatment	1, 5, 6	Perceived Benefits of Treatment (Chao 2005)

^a^Time Point 1 = baseline (0 months), 2 = intervention 1 (alarms, 3 months), 3 = intervention 2 (eyeGuide, 6 months), 4 = eyeGuide follow-up visit (8 months), 5 = intervention end (12 months), 6 = end of adherence monitoring (24 months, end of study)

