**Fig. 3 Fig3:**
[figure not shown]
Pilot study timeline

Eligible patients will participate in five more study visits. At the third study visit, 6 months from enrollment, participants will have their first 60-min eyeGuide counseling session with the glaucoma counselor and will take a 30-min survey. Their eye drop instillation will also be video-recorded. At the fourth study visit, 8 months from enrollment, participants will have their second 30-min eyeGuide counseling session and will take a 10-min survey. At their fifth study visit, 10 months from enrollment, they will have their final 30 min eyeGuide counseling session and have their eye drop instillation technique video-recorded. The intervention will end at the sixth study visit, 12 months from enrollment, where participants will come in to take a 45-min survey and undergo a 30-min semi-structured interview to obtain qualitative feedback about the eyeGuide program. Between the in-person eyeGuide counseling sessions, the glaucoma counselor will check-in with participants by telephone to update them on their adherence and discuss any issues they are having. These check-ins will take place more frequently at the beginning of the eyeGuide intervention, at 2 week intervals, and less frequently toward the end of the eyeGuide intervention (at 1 month intervals; Fig. 3). Participants will continue using their electronic medication monitors for an additional 12 months after the intervention has ended. At the seventh and final study visit, 24 months from enrollment, participants will return their electronic medication monitors and take a 45-min survey. Participants will receive a $35 stipend for each of their seven study visits and $35 for returning their adherence monitors.

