Secondary outcomes include comparing adherence measured by pharmacy refill data, self-report, and successful eye-drop instillation to electronic monitoring using Pearson’s correlations. Changes in glaucoma skills and energy for change will be assessed after each intervention component and at 1 and 2 years post-intervention and compared with paired *t* tests and McNemar’s tests for continuous and categorical measures. All analyses will be conducted with SAS software, version 9.4 (SAS Institute, Cary, NC, USA).

The semi-structured interviews will be recorded and transcribed verbatim. Two investigators will read the transcripts and identify major themes. The data will be interpreted qualitatively using grounded theory [86]. A code book will be generated defining codes for each theme. Two investigators will then code the transcripts. Any areas of disagreement will be discussed until consensus is reached or adjudicated by a third researcher [87]. The coded content will be tallied to weight the frequency of the themes. The transcripts will also be analyzed by participant group, those who did and those who did not improve from the intervention. Themes from these two groups will be compared in a joint display to try to identify reasons why the program was not successful among some participants to identify areas for programmatic improvement.

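### The month-8 knowledge test is labelled as following eyeGuide but falls mid-programme, and three of the five skill constructs lack the time points to separate the reminder period from the eyeGuide period

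*Protocol article*

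**What the plan says.** Under Secondary outcomes, the Protocol article fixes the timing of the knowledge test: "Glaucoma knowledge will be measured at the 3- and 8-month study visits, before and after the eyeGuide intervention, respectively". A further test follows at month 24.

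The Timeline section dates eyeGuide as follows:

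- Start: "At the third study visit, 6 months from enrollment, participants will have their first 60-min eyeGuide counseling session".
- Month 8: "At the fourth study visit, 8 months from enrollment, participants will have their second 30-min eyeGuide counseling session".
- Last session: "At their fifth study visit, 10 months from enrollment, they will have their final 30 min eyeGuide counseling session".
- End: "The intervention will end at the sixth study visit, 12 months from enrollment".

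The paragraph on satisfaction measures also places the close of eyeGuide at month 12. The footnote to Table 2 calls month 8 a follow-up visit within eyeGuide and month 12 the end of the intervention. The Component 1 and Component 2 text puts three months of automated reminders, from month 3 to month 6, ahead of eyeGuide.

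Secondary outcomes and Data analysis both plan to examine change in skills by component. Data analysis says this will be done "after each intervention component and at 1 and 2 years post-intervention". Two of the remaining skill schedules are sparser than that: "Goal setting will be measured at the baseline study visit, and the 12- and 24-month study visits", and "Confidence asking the physician questions will be assessed at the baseline visit and the 12-month study visit".

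**The concern.** The study delivers two components in sequence and wants to know what each one does. To describe a change by component, a skill needs a value near the start of reminders, one at month 6 (end of reminders, before the first counselling session) and one at month 12 (end of eyeGuide).

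The knowledge test has neither of the last two. A reader who follows the label would report the 3-to-8-month change as the before-and-after effect of eyeGuide. In fact it includes the whole reminder period and stops before the programme is complete. Goal setting and confidence in asking the physician questions have an end-of-eyeGuide value but nothing at the boundary between the components. Only one combined change, from baseline to month 12, can be computed for them. These constructs are among the proposed psychosocial mediators, so the by-component reporting of three of the five skills is at stake.

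**Working it through.** **1. Counselling dose: the plan's own figure first.** The inputs come from the last paragraph of Component 2: one 60-min session, two 30-min sessions and five 10-min calls.

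60 + 2 × 30 + 5 × 10 = 170 min, which matches the stated total.

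**2. Dose delivered by the month-8 visit.** Component 2 schedules calls every two weeks between the first two sessions, then monthly. Three calls between months 6 and 8, with two later ones (for example at months 9 and 11), would make up the five. The article text does not state this split, and Fig. 3 is not shown, so it is an assumption. The range for two to four calls is:

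| Calls before month 8 | Test before session 2 | Test after session 2 |
|---|---|---|
| 2 | 60 + 20 = 80 (47%) | 60 + 20 + 30 = 110 (65%) |
| 3 | 60 + 30 = 90 (53%) | 60 + 30 + 30 = 120 (71%) |
| 4 | 60 + 40 = 100 (59%) | 60 + 40 + 30 = 130 (76%) |

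Percentages are of 170 min. On in-person time alone the figure is 60/120 = 50% or 90/120 = 75%. Every row places month 8 mid-programme.

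**3. Calendar content of the 3-to-8-month window.** Reminders run from month 3 to month 6, so all 3 months are inside it. EyeGuide runs from month 6 to month 12, so 2 of its 6 months are inside it.

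**4. Schedules against component boundaries.** Months are from enrollment. The intervention ends at month 12, so 1 year after is 12 + 12 = month 24 and 2 years after is 12 + 24 = month 36.

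| Construct | Measured at | Month 6 | Month 12 | Month 24 | Month 36 |
|---|---|---|---|---|---|
| Knowledge | 3, 8, 24 | no | no | yes | no |
| Goal setting | 0, 12, 24 | no | yes | yes | no |
| Confidence asking questions | 0, 12 | no | yes | no | no |
| Perceived competence | 0, 6, 12, 24 | yes | yes | yes | no |
| Self-efficacy | 0, 6, 12, 24 | yes | yes | yes | no |
| Energy for change (both scales) | 0, 6, 12, 24 | yes | yes | yes | no |

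Three of the five skill constructs have no month-6 value. Knowledge also lacks month 12, and confidence also lacks the month-24 follow-up. No construct has a value at month 36, because the last visit is at month 24.

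**The case against.** Several replies have force.

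- **Month 3 does precede eyeGuide.** That is correct: only the second half of the label is wrong. Month 3 is also the useful pre-reminder value and should stay.
- **Reminders teach nothing.** As described, Component 1 consists of alerts, texts and automated calls, while education and action planning sit in eyeGuide. A knowledge gain between months 3 and 8 may therefore come mostly from eyeGuide. This is plausible, but it does not make month 8 the end of eyeGuide, and it leaves the promised change after each component without data.
- **Minutes are a weak proxy for knowledge.** This stands. The article does not say how education is divided across sessions, so the 47–76% range describes delivered time, not the share of the knowledge effect captured.
- **A full-programme contrast exists.** The month-24 test allows a 3-to-24-month knowledge change. This also stands, although that change includes a year of follow-up and does not separate the components.

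A reader might also infer that the mediation analysis fails. The documents do not support that: Data analysis specifies mixed models on slope over time, which fewer visits thin but do not make inestimable. Nor does the gap extend to all skills; perceived competence and self-efficacy follow the schedule the plan needs. Finally, the reference to 2 years post-intervention might be read as a planned comparison that will come up empty. The article elsewhere consistently gives one post-intervention year, so this is a wording slip, probably for 1 and 2 years from enrollment.

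**Conclusion.** The point holds, with limited scope. The month-8 knowledge value is mislabelled: it is taken at the second of three sessions, four months before eyeGuide ends. The 3-to-8-month change covers all of the reminder period plus about half to three quarters of the counselling minutes (53–71% with three prior calls, 47–76% with two to four; the spread also reflects whether the test comes before or after session 2). For knowledge, goal setting and confidence in asking questions, the reminder-period and eyeGuide-period changes cannot be estimated separately. One phrase in Data analysis needs correcting because it matches no visit.

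The primary outcome is monitored continuously and is untouched. Perceived competence, self-efficacy and both energy-for-change scales are also untouched, although their change from baseline to month 6 includes the three-month monitoring run-in as well as reminders.

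It would be too strong to say that better timing would let changes be attributed causally to a component. The article itself names the missing control arm as its main limitation. Extra time points separate periods; they do not establish cause.

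**What to change.** - **Knowledge:** keep months 3 and 24, add month 6 before the first session, and move the month-8 test to month 12. Correct the label accordingly.
- **Goal setting:** add the three items at month 6.
- **Confidence asking questions:** add the three items at month 6, and at month 24 for the follow-up comparison.
- **Data analysis wording:** state the later assessments as 12 and 24 months from enrollment, that is, the end of the intervention and 1 year after it.
- **Participants already past these visits:** label the month-8 knowledge value mid-programme, and report the 3-to-8-month change as covering reminders plus part of eyeGuide.

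Cost per participant: knowledge 2 × 10 = 20, goal setting 3, confidence 2 × 3 = 6, so 29 item administrations. Dropping the month-8 test removes 10, leaving 19 net. The visits at months 6, 12 and 24 already include surveys of 30, 45 and 45 minutes. A minor ethics amendment would be needed; the sample size does not change.

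### The glaucoma-knowledge test labelled as following eyeGuide falls mid-programme, at month 8, and no end-of-programme knowledge value is planned

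*Protocol article*

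**What the plan says.** The Secondary outcomes section gives the schedule and its label together: "Glaucoma knowledge will be measured at the 3- and 8-month study visits, before and after the eyeGuide intervention, respectively". A further test follows at month 24.

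The Timeline section places the programme differently:
- Start: "At the third study visit, 6 months from enrollment, participants will have their first 60-min eyeGuide counseling session".
- Middle: "At the fourth study visit, 8 months from enrollment, participants will have their second 30-min eyeGuide counseling session and will take a 10-min survey".
- Last session: "At their fifth study visit, 10 months from enrollment, they will have their final 30 min eyeGuide counseling session".
- End: "The intervention will end at the sixth study visit, 12 months from enrollment".

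The footnote to Table 2 agrees with the Timeline: "4 = eyeGuide follow-up visit (8 months), 5 = intervention end (12 months". The same footnote ties month 3 to the start of the reminders and month 6 to the start of eyeGuide. The Abstract describes the counselling programme as lasting six months.

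Glaucoma knowledge is one of five constructs that make up perceived glaucoma skills, a proposed mediator of adherence. Both Secondary outcomes and Data analysis promise an assessment of the change in skills once each intervention component has been given.

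**The concern.** The label and the timeline cannot both be right. If the label is followed into the report, a score taken while the programme is still running will be presented as the post-intervention result. Tailored education is a core part of eyeGuide, and knowledge is the skills measure closest to it, so this is a result readers will look for in a pilot meant to prepare a randomized trial.

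Three things are at stake:
- The gain at the end of the programme is not observed.
- With no value at month 6, the change over the reminder phase and the change over eyeGuide cannot be told apart.
- With no value between month 8 and month 24, a lower or higher month-24 score cannot be split into further gain during the rest of the programme and loss afterwards. The mediator models in Data analysis would likewise have no knowledge value at the end of the intervention.

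**Working it through.** **1. Measurement months of the five skills constructs (Secondary outcomes)**

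| Construct | Months | Month 6? | Month 12? |
|---|---|---|---|
| Perceived competence | 0, 6, 12, 24 | yes | yes |
| Glaucoma knowledge | 3, 8, 24 | no | **no** |
| Medication and instillation self-efficacy | 0, 6, 12, 24 | yes | yes |
| Goal setting | 0, 12, 24 | no | yes |
| Confidence asking questions | 0, 12 | no | yes |

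Knowledge alone lacks the value at the end of the intervention. Two other constructs also lack month 6, so that gap is not peculiar to knowledge.

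**2. How the protocol labels before and after elsewhere.** In Primary outcome, the video recordings before and at the end of eyeGuide are taken at visits 3 and 5, that is months 6 and 10. Satisfaction with information is measured at month 12, described as the conclusion of eyeGuide. Only the knowledge test uses months 3 and 8.

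**3. Total counselling time.** Component 2 gives one 60-minute session, two 30-minute sessions and five 10-minute calls: 60 + 2×30 + 5×10 = 170 min. This reproduces the stated total exactly.

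**4. Share delivered by the month-8 test.** Calls are fortnightly between the first two sessions, then monthly. Two months is about 8.7 weeks, so calls at weeks 2, 4 and 6 give three, and one at week 8 would make four. Three fits the total of five better, since it leaves two monthly calls for the rest of the programme. The article does not say whether the survey comes before or after that day's session, so both orders are shown.

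| Calls by month 8 | Test before session 2 | Test after session 2 |
|---|---|---|
| 3 | 60 + 30 = 90; 90/170 = 53% | 90 + 30 = 120; 120/170 = 71% |
| 4 | 60 + 40 = 100; 100/170 = 59% | 100 + 30 = 130; 130/170 = 76% |

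Between 24% and 47% of the minutes are still to come. Counting only in-person time (60 + 30 + 30 = 120 min), 60/120 = 50% or 90/120 = 75% has been delivered.

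**5. Calendar time.** Programme elapsed at month 8: (8 − 6)/(12 − 6) = 33%. The window from month 3 to month 8 lasts five months: (6 − 3)/5 = 60% reminders only and (8 − 6)/5 = 40% eyeGuide.

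**The case against.** The case for leaving this as a minor wording matter has several parts.

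- *Month 3 is before eyeGuide.* Correct. A reader might infer that the 3-to-8-month change does not measure eyeGuide at all. The protocol does not support that: the month-3 test precedes the first session, and the window contains the whole of that 60-minute session. The change is partial and not isolated, but it does include an eyeGuide effect.
- *Reminders are unlikely to raise a knowledge score.* A reader might also infer that the reminder phase biases the result. As described under Component 1, the reminders are alerts sent when a dose has not been taken, with no teaching content. The overlap is a weakness of attribution, not shown bias, and goal setting and confidence asking questions span even longer windows. This part of the point is secondary.
- *Minutes are a rough proxy for teaching.* The article places the teaching in the in-person sessions and gives the calls to adherence feedback and action plans. On in-person time the share is 50% to 75%, so the conclusion hardly changes. The 33% calendar figure, taken alone, understates how front-loaded the programme is.
- *Month 24 is still informative.* It is. Months 3 to 24 give the net long-term change, and months 8 to 24 show whether the mid-programme score holds. Neither gives the end-of-programme value.
- *An early test after the first session may have been intended.* Possibly, but the protocol does not say so.

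None of this removes the contradiction. Nor is it a detail left to a fuller document: the article states both the months and the label, and they conflict with its own timeline.

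**Conclusion.** The point holds: month 8 is mid-programme by the protocol's own account, and the test given then is wrongly labelled. The planned assessment of skills at the end of each component cannot be made for knowledge, because neither the end of the reminders nor the end of eyeGuide has a knowledge value.

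The 53% to 76% range rests on assuming three or four calls by month 8 and on the unstated order of survey and session. The contradiction itself rests on no assumption.

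The reach is limited to one of five constructs within one of two secondary mediators, in an uncontrolled pilot. It should be corrected, but it does not threaten the study's main result.

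**What to change.** Give the 10-item true/false test at month 6, before the first counselling session, and at month 12, and keep month 24. Define the eyeGuide change as month 6 to month 12 and retention as month 12 to month 24. The first pair then brackets the programme from 0 to 170 minutes and matches the schedule already used for perceived competence and self-efficacy. If month 3 is also kept, month 3 to month 6 gives the change over the reminder phase.

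The cost is ten items added to surveys already planned at those visits (30 minutes at month 6, 45 minutes at month 12) and one amended sentence. Both visits are already full: month 6 also has a 60-minute session and a video recording, and month 12 a 30-minute interview. The added burden is small but not nil.

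If the schedule cannot be changed, the minimum is to relabel month 8 as an interim value, to describe the 3-to-8-month change as reminders plus partial eyeGuide, and to state that no end-of-programme knowledge score is available. That costs only wording.
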